## Abstract

**Introduction:**

The decisions of withholding or withdrawing life-sustaining treatments are difficult to make in the context of emergency departments (EDs) because most patients are unable to communicate. Relatives are thus asked to participate in the decision‐making process, although they are unprepared to face such situations. We therefore aimed to develop a standardised intervention for announcing decisions of withholding or withdrawing life-sustaining treatments in EDs and assess the efficacy of the intervention on the stress of relatives.

**Methods and analysis:**

The DISCUSS trial is a multicentre stepped-wedge cluster randomised study and will be conducted at nine EDs in France. A standardised intervention based on human simulation will be codesigned with partner families and implemented at three levels: the relatives, the healthcare professionals (HCP) and the EDs. The intervention will be compared with a control based on treatment as usual. A total of 538 families are planned to be included: 269 in the intervention group and 269 in the control group. The primary endpoint will be the symptoms of post-traumatic stress disorder (PTSD) at 90 days. The secondary endpoints will be symptoms of PTSD at 7 and 30 days, diagnosis of PTSD at 90 days and anxiety and depression scores at 7, 30 and 90 days. Satisfaction regarding the training, the assertiveness in communication and real-life stress of HCPs will be measured at 90 days.

**Ethics and dissemination:**

This study was approved by the ethics committee Est III from Nancy and the French national data protection authority. All relatives and HCPs will be informed regarding the study objectives and data confidentiality. Written informed consent will be obtained from participants, as required by French law for this study type. The results from this study will be disseminated at conferences and in a peer-reviewed journal.

**Trial registration number:**

NCT06071078.

STRENGTHS AND LIMITATIONS OF THIS STUDYThe strategy proposed is based on a standardised intervention that will be implemented at three levels (healthcare professionals (HCP), relatives and the emergency department (ED)) and will be codesigned with partner families.The originality of the proposed protocol is the involvement of partner families, which has never been tested and the use of the Theoretical Domain Framework will enhance the expected efficacy of the training.A stepped-wedge randomised controlled trial provides a high level of evidence while adopting the pragmatic approach needed to study the implementation of training in practice.Another strength of this study is the use of a mixed methodology, including a qualitative component, to study the experiences of HCP and families in greater depth.The main limitation of the intervention will be the reproducibility and the adherence to the training in all EDs.

## Introduction

### Context of emergency departments (EDs)

 Death in the ED occurs in 0.3% to 0.5% of emergency admissions, representing approximately 26 000 deaths per year in France.^1^ For 80% of these deceased patients, a decision of withholding or withdrawing life-sustaining treatments was made in the ED.^1 2^ These decisions are complex in the context of EDs because data regarding patients’ medical history and previous functional limitations are often lacking. Moreover, most patients are unable to communicate or make decisions due to their clinical state and advance directives are only very rarely available. Nevertheless, ethical aspects must be respected and families are thus asked to participate in the decision‐making process concerning the withdrawal or withholding of life-sustaining treatments, although they are unprepared to face such situations. In addition, the short delay between ED admission and the decisions increases the stress and anxiety of families who are unprepared for the announcement. The lack of time, the inappropriate places to make announcements in the EDs and the lack of training also worsen the situation and add difficulty for healthcare professionals (HCP).^3^ Physicians facing these situations report a feeling of loneliness and being overwhelmed^3^ and both nurses and physicians report difficulties in communicating with relatives regarding such decisions.^4^

### Impact on relatives

The impact on relatives of the announcement of a decision to withdraw or withhold life-sustaining treatments has been widely explored in the context of intensive care units (ICU).^5 6^ In this setting, it has been shown that symptoms of anxiety and depression are correlated with the onset of post-traumatic stress disorder (PTSD), the symptoms of which were more important among the relatives of deceased patients having undergone a decision of withholding or withdrawing life-sustaining treatments and when the relatives were involved in the decision-making process.^7^ The impact on relatives in the context of EDs, however, has rarely been studied. In a previous study, we found that relatives displayed symptoms of anxiety and depression after the announcement, symptoms which persisted over time.^8^

### Strategies for reducing the impact on relatives

With the aim of preventing the onset of PTSD symptoms after death or a decision of withdrawing or withholding life-sustaining treatments, several studies have evaluated communication strategies in the ICU setting.^9^,^12^ For example, it has been shown that the training of nursing staff in communication skills or the use of a brochure for dealing with the families of patients who have died in the ICU reduces the incidence of PTSD symptoms among relatives.^9^ Human simulation is a pedagogical technique for learning interpersonal skills through role playing that has shown its effectiveness not only in communication training but also in developing empathy compared with the standardised patient method.^13^ The use of simulation has been demonstrated to teach end-of-life communication among health students^14^ and among HCP, with a positive impact on the families in the ICU.^15^

We therefore aimed to develop a standardised intervention using human simulation for announcing decisions of withholding or withdrawing life-sustaining treatments in EDs. We present here the protocol for the DISCUSS trial, a multicentre stepped-wedge cluster randomised trial evaluating the impact of a standardised intervention for announcing decisions of withholding or withdrawing life-sustaining treatments in EDs on the stress of relatives. Partner families will be involved in the design of the intervention, which will then be implemented at three levels: the HCP, the relatives and the ED. Involving patients and families as partners in research has been shown to improve the social acceptability of studies and facilitate knowledge transmission strategies among patients and HCP.^16^ Moreover, recommendations to promote patient involvement in emergency medicine research have recently been published.^16^ The group of Wright *et al* have also adapted the framework for patient partnership in research to the contextual challenges of the EDs for each stage of the research process, thus facilitating patient engagement. This practice, however, is not yet largely implemented in France.^17 18^

### Objectives

The main objective of the trial is to compare PTSD symptoms presented by families 90 days after an announcement of a decision to withhold or withdraw life-sustaining treatments in EDs between announcements made following the implementation of the standardised intervention and those made according to usual practices.

The secondary objectives are to study the efficacy of the standardised intervention on the following patient-reported outcomes: PTSD, anxiety, depression, families’ experiences of the announcement and impact on the socioprofessional life of family members during 90 days. We will also measure the efficacy of the standardised intervention on HCP satisfaction regarding the training, assertiveness in communication, self-confidence, real-life stress levels in the work environment, behavioural changes and the experience of the announcement from the HCP perspective. A process evaluation of the intervention implementation will be conducted using a mixed-method approach based on the Medical Research Council guidance.^19 20^ Semistructured interviews will be conducted to understand the barriers and facilitators perceived by the relatives and HCP.

## Methods and analysis

### Study design

The DISCUSS trial is a multicentre stepped-wedge cluster randomised study, which will be conducted at nine EDs in France. The nine EDs will be arranged into four groups, each group thus being composed of two to three EDs. The trial will be performed in five steps, and each group of clusters will be randomly assigned to one step. After a preintervention period (control), the intervention will be sequentially implemented in the groups at different times, according to a random allocation sequence generated by computer by the biostatistical team in charge of data analysis and blinded to group composition. All clusters will eventually receive the intervention (figure 1).

**Figure 1 F1:**
[figure not shown]
Study design and clusters randomization according to the different time periods.

The control group will be composed of relatives included in the preintervention period, and the intervention group will be composed of relatives included after the implementation of the intervention. No relative will be included during the transition periods corresponding to a 1-month period during which the intervention will be deployed in the ED.

For the qualitative analysis, semistructured interviews will be conducted with relatives: between 15 and 20 interviews will be planned depending on data saturation. This number is planned based on the available literature on data saturation.^21 22^ However, if new information emerges from the final interviews, additional interviews will be planned.

The reporting of the study protocol follows the Standard Protocol Items: Recommendations for Interventional Trials guidelines,^23^ and the description of the planned intervention is guided by the template for intervention description and replication checklist.^24^ Patient and public involvement is reported according to the GRIPP V.2 reporting checklist.^25^

### Setting and patients

The target population of relatives will be composed of designated trusted persons, family members or friends to whom the first announcement of a decision to withhold or withdraw life-sustaining treatments is made by a physician participating in the study. The study will include only adult patients and adult relatives. For each patient, one relative will be included. Another emergency physician who does not make the announcement will inform the patients and their relatives and obtain their consent before their inclusion in the study. Relatives for whom the announcement is made entirely by telephone will not be included.

### Design of a standardised three-level intervention

During the first phase of the protocol, the detailed content of the intervention will be codesigned with partner families who have previously experienced an announcement of a decision of withholding or withdrawing life-sustaining treatments in the ED. Semistructured interviews with the partner families and two workshops will be conducted by professionals trained in qualitative research to develop and validate the intervention. The intervention will also be designed according to national and international recommendations^23^,^25^ and using the Theoretical Domain Framework (TDF),^26 27^ specifically guided by the following dimensions: knowledge, skills, social/professional role and identity, beliefs about capabilities, optimism, intentions, environmental context and emotion.

### Intervention implementation

The intervention will then be deployed at three levels. At the level of the HCP (physicians and nurses), the intervention will consist in a two-step human simulation training approach. First, two pairs of HCP (one physician and one nurse) will be trained in a simulation centre by a trainer specialised in simulation concerning decisions of withholding or withdrawing life-sustaining treatments. The trained HCP will then implement the training in situ in the ED with the help of the specialised trainer. The scenarios used in the human simulation training will be constructed during the first phase with the partner families based on their experiences. The intervention will also include video testimonials from partner families and a training manual including all the objectives and skills targeted by the training, which will be made available electronically to all HCP. At the level of the relatives, an information booklet on the decision-making process for withdrawing or withholding life-sustaining treatments and end-of-life care in the context of EDs, codeveloped with the partner families, will be given to the relatives included in the study. Finally, at the level of the ED, changes will be made to provide a dedicated room for the announcement. Time will be allocated specifically for making the announcement, which will be made by a team of HCP (a physician and a nurse).

### Control (treatment as usual)

The control group will be composed of relatives who have received an announcement of a decision of withholding or withdrawing life-sustaining treatments from an HCP who has not undergone the standardised intervention, that is, before the deployment of the training in the ED.

A survey of the usual practices for the announcement of decisions of withholding or withdrawing life-sustaining treatments in each centre will be carried out before the beginning of the intervention. More specifically, information regarding possible training received by the HCP on the subject, existence of an announcement procedure and/or a place dedicated to the announcement in the ED, the presence of a psychologist intervening during the announcements and the possible recourse to religious representatives will be collected.

### Measurement of patient outcomes

The study schedule reporting the time points for data collection is presented in online supplemental table 1.

### Primary outcome

Symptoms of PTSD at 90 days will be measured by the Impact of Events Scale (IES),^28^ a 15-item self-administered questionnaire validated in French,^29^ which measures symptoms of intrusion, avoidance and hyperarousal experienced over the past 7 days. Each item is graded from 0 to 4 and the final score ranges from 0 to 75. Higher scores reflect the greater presence of symptoms, and a score above 30 indicates the presence of symptoms suggestive of PTSD requiring referral for treatment. For all the subjects included, the questionnaire will be carried out over the phone, by a psychologist from the coordinating centre blinded to group allocation, 90 days after the announcement in the ED.

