### Sample size

A mean IES of 33 is expected at 90 days during the control periods (SD of 9) and a relative reduction of 12% of the mean score is expected with the intervention. Under thess hypotheses, for a 90% power and a 5% two-sided alpha level, 216 families would be necessary. By considering an intraclass correlation coefficient of 0.35, 9 EDs divided into 4 groups and 15% of loss to follow-up, a total of 538 families will be necessary.

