### Statistical analysis

The IES Score will be analysed by a linear mixed effect model. It will consider as fixed effect, the intervention (period with or without the intervention), the measurement time point (7, 30 and 90 days), and an interaction between time point and period. The model will also be adjusted on the following factors:

Regarding the patient: age, institutionalised patient, advance directives, death of the patient during the 90 days.Regarding the relatives: age, sex, relationship with the patient, lifestyle (single or in a relationship), frequency of contact with the patient over the past 6 months, history of psychological or psychiatric care, religious beliefs.Regarding the ED at the time of the announcement: work overload, doctor/nurse/patient ratio in the ED at the time of the announcement.

The model will include as random effect, a random intercept by ED and a random intercept and slope by family nested in the ED level. The effect of the intervention at 90 days will be recalculated from the coefficients of the model; it will be quantified by the difference of mean with the associated 95% CI and tested by a Wald test. A period effect will be tested in the model. A secondary analysis for the primary endpoint will be performed by considering IES as a binary variable, a value above 30 indicating a high risk of PTSD. The analysis will be similar to the one previously described, but performed using a mixed effect logistic regression model.

The analysis of PTSD at 7 and 30 days will be performed by calculating the effect of the intervention from the coefficients of the aforementioned model.

The analysis of anxiety and depression will be performed similarly to one of the primary endpoint and will focus specifically on the effect of the intervention at day 7 and on the effect of the intervention on the slope. A binary analysis will also be performed, by considering anxiety or depression when the HADS scores are above 8.

The analysis of PTSD symptoms at 90 days will be performed by a mixed effect logistic regression model, considering only the ED as random intercept. The comparison of the proportion of relatives with at least one work absenteeism will be performed by a mixed effect logistic regression model. The percentages of relatives for whom the announcement was considered smooth will be compared. A threshold of 0.05 will be considered significant. Analyses will be performed using R and SAS software (version 9.4).

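### The primary outcome scale is defined in two incompatible ways: 15 items graded 0 to 4 total at most 60, not the stated 75

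*Protocol article*

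**What the plan says.** The Primary outcome section of the protocol article measures PTSD symptoms at 90 days with the IES, "a 15-item self-administered questionnaire validated in French". On scoring it states: "Each item is graded from 0 to 4 and the final score ranges from 0 to 75". It then attaches a fixed threshold to the total: "a score above 30 indicates the presence of symptoms suggestive of PTSD requiring referral for treatment".

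The Statistical analysis section analyses the IES score at 7, 30 and 90 days in one linear mixed model, with the 90-day effect tested by a Wald test. It adds a secondary analysis of the primary endpoint, "considering IES as a binary variable, a value above 30 indicating a high risk of PTSD".

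The Sample size section plans on a control mean of 33 and an SD of 9 at 90 days, and "a relative reduction of 12% of the mean score is expected with the intervention". It does not say which score range these values refer to. No section gives a weighting or transformation of the items.

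**The concern.** Number of items, item grading and total range are three facts about one score, and any two of them fix the third. Here they disagree, for the primary endpoint.

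A relative change in a mean does not depend on the units, but an absolute cut-off does. The value 30 is half of a 60-point maximum and two fifths of a 75-point maximum. If items were coded as the article says (0 to 4) while the cut-off came from a 0 to 75 scoring, the binary analysis and the referral statement would be read on a scale other than the one they were set for. A difference reported in points would be just as ambiguous. The Data collection section says inclusion began in January 2024, so scores are already being recorded under one coding or another.

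**Working it through.** **Inputs.** Primary outcome section: 15 items, grades 0 to 4, total 0 to 75, cut-off above 30. Sample size section: mean 33, SD 9, 12% relative reduction, 90% power, two-sided 5%, 216 families unadjusted; intraclass correlation 0.35, 9 EDs in 4 groups, 15% loss, 538 in total.

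**1. Score range.** Maximum = items × top grade.
- As stated: 15 × 4 = 60, against 75. Not reproduced.
- Top grade needed for 75: 75 / 15 = 5.
- Items needed for 75 at a top grade of 4: 75 / 4 = 18.75, which is not a whole number.

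So with 15 items, either the range is 0 to 60 or the top grade is 5.

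**2. Do the planning figures rule out either range?** No. A mean of 33, an SD of 9 and a cut-off of 30 fit inside both 0 to 60 and 0 to 75.

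**3. The plan's own sample size.** Planned difference = 0.12 × 33 = 3.96 (33 to 29.04). Standardised effect = 3.96 / 9 = 0.44.
- n per arm = 2 × (1.960 + 1.282)² × 9² / 3.96² ≈ 108.5, rounded up to 109, so 218 in total against the stated 216. Reproduced to within 2.
- Stepped-wedge design effect with k = 4 steps, one baseline period and one measurement per step, and an assumed n = 10 families per ED per period: [1 + 0.35 × (40 + 10 − 1)] / [1 + 0.35 × (20 + 10 − 1)] × 3 × (1 − 0.35) / [2 × (4 − 1/4)] = (18.15 / 11.15) × 0.26 = 0.4232.
- 216 × 5 periods × 0.4232 = 457.1; 457.1 / 0.85 = 537.7, against the stated 538. Reproduced under that assumption.

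**4. Does the scale matter for N?** Multiply every score by 60 / 75 = 0.8: mean 26.4, SD 7.2, difference 3.168. The standardised effect is 3.168 / 7.2 = 0.44, and N is again 218. The Wald statistic for the treatment effect is likewise unchanged by a common linear rescale.

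**5. Does the scale matter for the cut-off?** Illustration only. Assume normal scores, planning values on 0 to 75, data collected on a scale uniformly compressed by 0.8, and the cut-off left at 30. Share above 30 = 1 − Φ((30 − mean) / SD).

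| | Planning values as stated | Compressed by 0.8 |
|---|---|---|
| Control | mean 33, SD 9: 63.1% | mean 26.4, SD 7.2: 30.9% |
| Intervention | mean 29.04, SD 9: 45.8% | mean 23.232, SD 7.2: 17.4% |

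Under these assumptions the share classified as high risk falls by about half in control and by more in the intervention periods.

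**The case against.** The strongest reply is that this is a one-digit slip in a condensed journal article (a 4 printed for a 5, or 75 for 60), with no effect on the trial. Much of that stands. The cut-off is given consistently in two sections, the primary analysis uses the continuous score, and the same questionnaire would be coded the same way in both periods, so no bias between arms is shown. The eCRF is not shown, and nothing says it carries the error.

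Three stronger readings are tempting, and the article supports none of them.

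- A reader might infer that the cut-off and planning values have no scale at all. They fit either range; what is missing is the link to one of the two.
- A reader might infer lost power, because the planned difference would shrink from 3.96 to 3.17 points. The SD shrinks with it, so N does not move. N would change only if the effect and the SD came from different scorings. For example, a difference of 3.168 with an SD of 9 would need 340 families unadjusted, and 109 per arm would give 73.8% power. Nothing in the article indicates such a mix.
- A reader might take the drop from 63% to 31% as a predicted result. It needs every assumption listed with it. If the item grade is the misprint, or if all figures come from 0 to 4 scoring, nothing shifts.

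What the reply does not remove is the contradiction. The article cannot show which number is wrong, and the scoring of a primary endpoint should not be left to guesswork.

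**Conclusion.** The point holds in a limited form. The Primary outcome section defines the IES total in two incompatible ways, with a maximum of 60 or of 75, and no other section settles which applies or which one the cut-off of 30, the mean of 33 and the SD of 9 belong to.

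The figures 216 and 538 and the Wald test on the continuous score are not shown to be wrong, provided the mean and SD share one scale and the two scorings differ only by a linear factor. The exposed elements are the meaning of a difference in points, the binary analysis at 30 and the referral statement. The possible size for the binary analysis is illustrated by 31% against 63% above the cut-off in control, which is conditional and not a forecast. The scoring should be corrected before analysis, because a choice of scoring made once results are known would be open to challenge.

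**What to change.** - Reconcile the item grades and total range in the Primary outcome section with the scoring of the questionnaire version actually administered, so that 15 times the top grade equals the stated maximum.
- Confirm, with the source, that the cut-off of 30, the planning mean and the SD come from that same scoring, and reconcile the Primary outcome, Sample size and Statistical analysis sections accordingly. Which threshold should govern referral is for the sponsor to settle, not this review.
- Check the item codes programmed in the eCRF against the corrected text.
- Only if they do not match, re-score the 7-, 30- and 90-day totals from stored item responses before analysis, and document the change.

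The cost is a text correction and an eCRF check, plus a programmed re-score in the worst case. No additional families are needed.
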